# Evaluation of the safety and efficacy of a Fuling-Zexie decoction for people with asymptomatic hyperuricemia: protocol for a prospective, double-blinded, randomized, placebo-controlled clinical trial

**DOI:** 10.1186/s13063-022-06479-3

**Published:** 2022-06-20

**Keywords:** Fuling-Zexie decoction, Asymptomatic hyperuricemia, Double-blinded, Randomized, Placebo-controlled

## Abstract

**Background:**

Hyperuricemia increases the risk of gout and cardiovascular complications, and how to manage asymptomatic hyperuricemia is controversial. Randomized controlled trials and comparative studies are needed to guide management and treatment. Studies show that Chinese medicine can decrease uric acid through multiple targets, but many of these studies have been conducted in animals because of the lack of a consistent prescription and mechanism. Therefore, we designed this research to study whether Chinese medicine is truly effective and which target is essential by using an approved prescription of a Fuling-Zexie decoction to further guide large sample experiments to determine whether Chinese medicine can reduce the long-term incidence of gout and cardiovascular events.

**Methods:**

This pilot study is a prospective, double-blinded, randomized, placebo-controlled clinical trial developed from March 2020 to December 2021. Thirty people with asymptomatic hyperuricemia will be recruited and assigned to either the Chinese medicine group or placebo group, and each group will have 15 subjects. During the 12-week observation period, there will be 4 visits. The decline in uric acid is the main outcome measure, and urinary uric acid, inflammatory biomarkers, and other indices that may be involved in lowering uric acid are the secondary outcome measures.

**Discussion:**

This study will probe the effect of Chinese medicine treatment on hyperuricemia and explore possible therapeutic mechanisms. By performing this trial, we hope to provide evidence and data to support further large clinical studies.

**Trial registration:**

ChiCTR2000038575. Registered on September 24, 2020.

**Supplementary Information:**

The online version contains supplementary material available at 10.1186/s13063-022-06479-3.

## Background

As living standards rise and dietary habits change, the prevalence of hyperuricemia has increased [1], especially in China [2]. It has become the second most common metabolic disease after diabetes mellitus and affects 133 persons per 1000 inhabitants in mainland China (the morbidity for men is 19.4%, and 7.9% for women) [3]. Meanwhile, the prevalence rate is higher in cities than in rural areas, and statistics show that the incidence of hyperuricemia in elderly individuals in Guangzhou and Beijing is 13.2% and 17.6%, respectively [4]. Hyperuricemia may eventually lead to gout and augment the risk of hypertension and other cardiovascular diseases [5]. However, there is no consensus on the management of asymptomatic hyperuricemia, and it remains controversial [6]. Chinese and Japanese guidelines recommend considering drug therapy when people have a serum urate level of no less than 9.0 mg/dL or 8.0 mg/dL with complications to prevent gout and cardiovascular or renal impairment [7, 8]. India’s Integrated Diabetes & Endocrine Academy (IDEA) has similar opinions [9], while asymptomatic hyperuricemia should only be treated with nonpharmacological treatment, which is the general consensus in the USA and Europe [10, 11]. The Asia-Pacific League of Associations for Rheumatology recommends against urate-lowering therapy for people with asymptomatic hyperuricemia and hypertension and gives no specific recommendations for people with asymptomatic hyperuricemia and chronic kidney disease due to insufficient evidence [12]. There are few studies on the treatment of asymptomatic hyperuricemia, including drug and nondrug treatments. These studies indicate benefits in treating people with asymptomatic hyperuricemia combined with insulin resistance or type 2 diabetes [13, 14] and an opposite result in mitigating the decline in kidney function [15, 16]. There is a need to conduct more research.

Influenced by the Chinese culture of “nipping problems in the bud,” people with hyperuricemia seek early interventions to prevent progression to gout and other diseases. Nonetheless, they do not prefer uric acid-lowering drugs, as someone with hyperuricemia is considered “not ill.” Thus, many people seek out Chinese medicine treatments. There have been randomized, double-blind, placebo-controlled trial on acupuncture for asymptomatic hyperuricemia [17], but no studies on Chinese medicine have been conducted.

Some animal studies have shown that Chinese medicine can lower uric acid levels, relieve symptoms and reduce the frequency of gout attacks [18–24]. The mechanism of Chinese medicine is complex and not yet clear. Some studies indicate that Chinese medicine may promote uric acid excretion [18–20]. Other studies have shown that Chinese medicine can modulate the levels of inflammatory cytokines [21–24]. Evidence also suggests that Chinese medicine inhibits the synthesis of uric acid [25, 26]. Therefore, our trial will test subjects’ uric acid excretion capacity and inflammation index. Recently, trials have found evidence for a difference in intestinal microecology between hyperuricemic people and healthy people [27, 28]. Experiments conducted in rats have shown that Chinese medicine has a certain influence on the composition of intestinal flora [29, 30]. Therefore, intestinal microecology before or after Chinese medicine treatment is another potential target of interest.

Evaluating the efficacy of Chinese medicine treatments and developing effective treatments for asymptomatic patients with hyperuricemia is difficult because Chinese medicine treats patients based on syndrome differentiation rather than disease differentiation; thus, the recipes for Chinese medicine for people may vary in composition. Therefore, it is essential to establish syndrome standards. Due to the lack of relevant literature and research, we gathered information on classic Chinese medicine by consulting Chinese medicine experts and combining their clinical experience to reach a consensus that for people with hyperuricemia in Guangdong Province, dampness syndrome is the main affliction.

We designed questionnaires that were completed by 11 people with hyperuricemia using an electronic questionnaire system. The results showed that all 11 cases were consistent with the clinical manifestations of dampness syndrome. Eight individuals had the manifestations of cold-dampness syndrome, and 3 showed the manifestations of dampness-hot syndrome. The minimum dampness score was 43, the maximum was 104, and the average was 70.09 ± 17.56. In summary of the 11 cases, 54.5% had a superficial syndrome. Based on clinical experience and combining the concept in Chinese medicine that “the beginning of disease is in the grain of skin and the texture of the subcutaneous flesh” and guided by the Chinese medicine theory of preventive treatment of diseases combined with the opinions of many classic Chinese medicine experts, we suggested the treatment viewpoint of “treating metabolic diseases from the exterior at the early stage.” We Choose the “Fuling-Zexie decoction,” which is specific to Taiyang-YangMing-Taiyin = combination diseases, as the main prescription for cold dampness, in the formula (see Table 1 [31]): Fuling and Baizhu can dissolve the wetness inside; both Guizhi and Shengjiang work on the exterior to treat the disease in and out simultaneously and pushes the wetness out with Zexie together.

**Table 1 Tab1:** The ingredients of the Fuling-Zexie decoction

Chinese name	English name	Latin name	Function (in Chinese medicine theory) [31]	Medicinal part	Dosage (g)
Fu ling	Tuckahoe	*Poria cocos (Schw.) Wolf*	Inducing diuresis to drain dampness; strengthening spleen	Dry sclerotia	48
Ze xie	Rhizoma alismatis	*Alisma plantago-aquati ca Linn*	Inducing diuresis to drain dampness; discharge heat	Dry tuber	24
Bai zhu	Largehead Atractylodes	*Atractylodes macrocephala Koidz*	Benefiting vital energy and invigorating the spleen; drying dampness	Tuber root	18
Gui zhi	Cassia twig	*Cinnamomum cassia Presl*	Resolving the flesh and sweating; warming the channels to free the networks vessels; reinforcing yang and activating vital energy	Dry twigs	12
Sheng gancao	Raw Licorice	*Glycyrrhiza uralensis Fisch*	Nourishing spleen and benefiting vital energy; moderating the property of herbs	Dry root	12
Sheng jiang	Fresh ginger	*Zingiber of icinale Rosc*	Resolving the exterior; dissipating dampness	Rhizome	2

## Methods and design

### Study objective

The objectives of the experiment are to study the efficacy and safety data of Chinese medicine therapy for dampness syndrome for hyperuricemia and to screen possible related small molecules/microbial material bases.

### Study design

This is a 12-week, single-center, prospective, double-blinded, randomized, placebo-controlled clinical trial. We used the SPIRIT reporting guidelines to perfect the protocol [32], from March 2020 to December 2021. Thirty individuals with asymptomatic hyperuricemia will be randomly assigned to receive Chinese medicine or a placebo at a 1:1 ratio (Figs. 1 and 2).

**Fig. 1 Fig1:**
[figure not shown]
Flow diagram for the study

**Fig. 2 Fig2:**
[figure not shown]
Participant timeline

### Sample size

This study will enroll 30 subjects. Further large-scale RCT trials will estimate the size of the sample according to the results of the main outcome indicators obtained from this study and use the sample content estimation formula to compare the two means to calculate the sample content, *α* = 0.025, *β* = 0.2. The sample size ratio of the test group and control group is 1. The follow-up rate is set according to the pre-experiment follow-up rate.

### Recruitment

Most asymptomatic patients with hyperuricemia do not seek medical attention, so we will recruit subjects through recruitment advertisements. The advertisements will be placed in the hospital building and be announced through the hospital’s official account.

### Study setting

The Guangdong Provincial Hospital of Chinese Medicine will be the only study setting.

### The study’s key problem

Dampness is involved with the development of hyperuricemia. The key to preventing gout, cardiovascular disease, and urate nephropathy is controlling the serum uric acid level. Can Chinese medicine improve the outcomes of the population with hyperuricemia population and reach the goal of early prevention of disease?

### Eligibility criteria

Inclusion criteria:Aged between 18 and 75 years (including 18 years and 75 years of age);Meet the diagnosis of asymptomatic hyperuricemia;Meet the dampness syndrome inclusion criteria;Sign informed consent.

Exclusion criteria:Secondary hyperuricemia, for instance, secondary to malignancy, hemopathy, nephropathy, and chronic intoxication;History of alcoholism without abstinence in the last 3 months;One or more attacks of gout arthritis in the past;Received urate-lowering drugs or drugs that may increase serum uric acid in the last 4 weeks: (1) antituberculotic drugs, such as pyrazinamide/ethambutanol/isoniazid, (2) low-dose aspirin, (3) loop diuretics, thiazide diuretics and blood pressure medications containing diuretics, (4) niacin, (5) large doses of vitamin C, (6) chemotherapeutic drugs, and (7) cyclosporin;Pregnancy or lactation, or the possibility of conception but failure to use effective contraception;Alanine aminotransferase, aspartate aminotransferase or creatinine levels 2 times or more than the normal value;Serious organic lesions, mental disorders or other reasons a person cannot cooperate with treatment;Allergies or no reaction to the test drug ingredients.

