### Elimination and termination criteria

The elimination criteria are as follows: (1) serious violation of exclusion standards after enrollment, (2) not completing the experimental drug administration during the experimental period as required after enrollment, and (3) incomplete one-month follow-up and no test records available for evaluation.

The termination criteria are as follows: (1) a gout attack, (2) severe adverse events, (3) condition deteriorated and required urgent medical attention, (4) the researcher recommended test termination because of the safety of the subjects, and (5) people unwilling to continue to participate in this study for personal reasons.

We will keep in touch with the subjects who drop out to observe any subsequent adverse events and collect data.

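### The 4-week prior-treatment exclusion does not name Chinese medicine, the treatment the protocol says many of these people seek, so recent herbal users can enter with an already treated week-0 uric acid

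*Protocol article*

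**What the plan says.** The exclusion criteria (Eligibility criteria) bar anyone who "Received urate-lowering drugs or drugs that may increase serum uric acid in the last 4 weeks". Seven numbered items follow, from antituberculotic drugs to cyclosporin, and include niacin and high-dose vitamin C. No herbal decoction, granule or Chinese patent medicine is among them.

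The Background says of the target population that "they do not prefer uric acid-lowering drugs, as someone with hyperuricemia is considered “not ill.” Thus, many people seek out Chinese medicine treatments". It also sets out why Chinese medicine might work: "Some animal studies have shown that Chinese medicine can lower uric acid levels", with further suggestions that it raises uric acid excretion, changes inflammatory cytokines and alters intestinal flora.

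On where subjects come from, Study setting says "The Guangdong Provincial Hospital of Chinese Medicine will be the only study setting". Under Recruitment, "The advertisements will be placed in the hospital building" and a notice also goes out through the hospital's official account.

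The primary outcome is the fall in serum uric acid, compared between two groups of 15. Under Sample size, the main-outcome result of this pilot is to be used to size a later, larger trial.

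**The concern.** The criterion screens for the treatment that the protocol says its population does not favour. It is silent on the treatment that the protocol says many of them seek, which is also the class under test. The Background sets the two side by side as alternatives, so a site has no clear instruction to treat a formula taken for dampness as a urate-lowering drug. As written, a person who took such a formula until shortly before week 0 can be enrolled.

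The outcome is a change from week 0. If that value is already lowered by an outside formula, the change mixes the effect of study treatment with the loss of the earlier effect. The baselines for excretion, inflammatory markers, metabolites and intestinal flora are open to the same disturbance. The pilot's mean difference and standard deviation then feed the sample size of the next trial.

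**Working it through.** **Figures in the plan.** The article gives 30 subjects at 1:1 (15 per arm) and two-sided alpha 0.05. It gives no effect size, standard deviation or power for this pilot, so 30 cannot be reproduced. It gives no rate of herbal use beyond saying that many people seek it. Everything below is therefore an illustration under stated assumptions.

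**Reference case.** With 15 per arm and two-sided alpha 0.05, a t-test has 80% power at a standardised difference of 1.06. Write D = 1.06, in units of the SD of the change score.

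**A. Prior use that stops at week 0** (what the eligibility criterion governs). Assume that the outside formula is as effective as the study decoction and that its effect has gone by week 12. Expected decrease from week 0:

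| | Active | Placebo | Difference |
|---|---|---|---|
| Not a prior user | D | 0 | D |
| Prior user | 0 | −D | D |

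The difference is D in both rows, so the randomised contrast is not biased. If a share p of subjects are prior users, the mixture adds p(1 − p)D² to the variance within each arm. The standardised difference becomes D / √(1 + p(1 − p)D²), with D² = 1.1236:

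| p | Added variance | SD ratio | Standardised difference | Power, 15 per arm |
|---|---|---|---|---|
| 10% | 0.09 × 1.1236 = 0.10 | 1.05 | 1.01 | 76% |
| 20% | 0.16 × 1.1236 = 0.18 | 1.09 | 0.98 | 73% |
| 30% | 0.21 × 1.1236 = 0.24 | 1.11 | 0.95 | 71% |
| 40% | 0.24 × 1.1236 = 0.27 | 1.13 | 0.94 | 70% |

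**B. Chance imbalance.** This is how the extra noise in A shows itself in one realised trial, not a second loss on top of it. Treat the 15:15 split as a simple random draw (hypergeometric). With 6, 9 or 12 prior users among 30 (20%, 30%, 40%), the chance that the arms differ by at least 4 users is 17%, 11% and 26%. The middle value is low only because 9 is odd, so the difference must be at least 5; for a difference of at least 3 it is 43%. A difference of 4 users moves the estimated contrast by 4/15 × D = 0.27D, in either direction.

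**C. Outside use that continues during the 12 weeks.** Assume a share c in both arms, the same effect as the study decoction, and no added effect in the active arm. The contrast becomes (1 − c)D:

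| c | (1 − c) × 1.06 | Power, 15 per arm |
|---|---|---|
| 10% | 0.95 | 71% |
| 20% | 0.85 | 61% |
| 30% | 0.74 | 50% |
| 40% | 0.64 | 39% |

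Only C moves the contrast towards zero, and a washout before entry does not govern it.

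**The case against.** A reader might infer that the gap biases the trial towards no effect because treated people enter both arms. The documents do not support that. Table A shows that prior use stopped at week 0 leaves the expected contrast unchanged; dilution arises only in case C.

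A reader might also infer that nothing stops placebo subjects from taking another decoction during the trial, since elimination covers "serious violation of exclusion standards after enrollment" and herbal use is not an exclusion standard. That can be said of the article only. A rule on concomitant treatment is commonly left to the full protocol (version 1.4 is cited under Trial status), which is not shown. Its absence here is not a finding.

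Three further points reduce the size of the concern. The phrase urate-lowering drugs is open-ended, and the article calls its own herbal product a drug in several places, so a site could read it to cover a herbal product taken for uric acid. Recruitment says that most people with the condition do not seek medical attention, so many recruits may be untreated. Entrants must also meet the diagnosis of hyperuricemia, which keeps out anyone whose uric acid has been brought to normal.

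What remains is that the list is printed in detail and the Background treats the two kinds of treatment as distinct. Formulas taken for dampness and not for uric acid are not clearly caught by any reading.

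**Conclusion.** The criterion is drawn too narrowly for the population that the protocol describes. Recent herbal users can enter with an already treated week-0 uric acid. In expectation this leaves the randomised comparison unbiased; it costs precision, allows chance imbalance at 15 per arm, and disturbs the baseline of the mechanistic outcomes. If 20% to 40% were prior users of an equally effective formula that wears off by week 12, power would fall from 80% to between 73% and 70%. The inflated SD would also carry into the planning of the later trial. A weaker outside formula would do less.

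The larger losses in table C depend on continued use during the trial, which the article neither establishes nor rules out. The true frequency of either kind of use is unknown. The point is modest in size, but the change is cheap and worth making.

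**What to change.** Extend the existing prior-treatment exclusion to name Chinese herbal medicine and Chinese patent medicine. The 4-week window already in the criterion is the natural default; its length for herbal products is for the investigators to confirm. Record prior use at baseline, record any outside use on the subject log card that the protocol already has, and report both by arm.

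State that subjects with outside use stay in the analysis as randomised. This needs saying because, once herbal use is an exclusion standard, the first elimination criterion could otherwise be used to remove them.

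Trial status gives an enrolment period of March to August 2021. For subjects already enrolled, ask about prior and outside use retrospectively where possible and report it by arm; the eligibility wording then applies to the later trial.

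The cost is one eligibility line, one baseline question and one log-card item. The downside is that some recent herbal users wait or are not enrolled.

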### Randomization and allocation

Adopting simple block group randomization, the allocation ratio will be 1:1. SAS9.2 PROC PLAN will be used to carry out procedure coding and random sequence generation by the methodology team.

The random distribution results will be released through the interactive network response random distribution system for clinical research in Guangdong Provincial Hospital of Chinese Medicine. The random assignment table in the random center will be kept strictly confidential until the end of the study.

After the patients are screened as qualified subjects and have given informed consent, the clinicians apply for the randomization system to obtain the randomization results on the internet. Physicians will execute the results according to random grouping and print and paste them on the corresponding position of the case report form (CRF).

### Blinding

A double-blinded, placebo-controlled design was adopted, and both the investigators and the subjects will be blinded. All data will be evaluated and statistically processed by a third party after clinical research.

The trial will be unblinded if there is a serious adverse event that may be related to the experimental drug, so we can know which group the subject was enrolled in to decide the rescue plan. The trial would be unblinded in the presence of the principal investigators and funders. The time, reason, and procedure of the unblinding and the researchers involved in the unblinding would be recorded. After the trial is unblinded, the subject would be terminated from the study, the experimental data would be included in the safety analysis dataset, and the subject would be given timely treatment and follow-up.

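### The emergency code break is tied to the presence of the principal investigators and funders, which its one-subject purpose does not need and which shows the arm to investigators meant to stay blinded

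*Protocol article*

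**What the plan says.** All the relevant text is in the protocol article.

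- **Who is blinded (Blinding):** "both the investigators and the subjects will be blinded". Funders are not named.
- **Trigger (Blinding):** "The trial will be unblinded if there is a serious adverse event that may be related to the experimental drug".
- **Purpose (Blinding):** "so we can know which group the subject was enrolled in to decide the rescue plan".
- **Procedure (Blinding):** "The trial would be unblinded in the presence of the principal investigators and funders". The time, reason, procedure and researchers involved are to be recorded.
- **Consequence (Blinding):** "After the trial is unblinded, the subject would be terminated from the study, the experimental data would be included in the safety analysis dataset". Timely treatment and follow-up of that subject are also promised.
- **Allocation (Randomization and allocation):** "Adopting simple block group randomization, the allocation ratio will be 1:1". Block size is not given. Results are released through an interactive network system, and "The random assignment table in the random center will be kept strictly confidential until the end of the study".
- **Size (Sample size):** "This study will enroll 30 subjects".

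**The concern.** The purpose and the procedure do not fit each other. The purpose is urgent and concerns one person. The procedure brings in several parties, one of which, the funders, has no clinical role anywhere in the article. If staff follow the sentence literally, access to safety information depends on who can attend.

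The procedure also sits badly with the blind. Principal investigators are investigators, the same section says investigators are blinded, and nothing in the text keeps the arm from those who attend.

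At stake are prompt access to one subject's allocation and, to a lesser degree, the blind for subjects who remain. Some secondary outcomes rest on judgement (the Chinese syndrome score and tongue diagnosis). So may the dampness-heat evaluation, which triggers a switch of intervention. A rater who can guess arms could be influenced on these.

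**Working it through.** The plan gives no figure to reproduce on this point, so the main check is textual.

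**1. Purpose against procedure.** Purpose: learn one subject's group to guide rescue. Procedure: do so with the principal investigators and funders present. The purpose needs only the person managing the event and a source for the code. The attendance condition adds a dependency that the purpose does not require. The article gives no timing, so the dependency can be shown but a delay cannot.

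**2. Blinded parties against parties present.**
- Principal investigators: covered by the statement that investigators are blinded, yet present at the code break. This is a conflict inside one section.
- Funders: not covered by that statement. Their presence is a design judgement, not a contradiction.

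**3. Trial or subject.** The trigger and procedure sentences speak of unblinding the trial. The purpose and consequence sentences speak of the subject. Context favours the one-subject meaning, but the wording should say so.

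**4. How far one disclosure can reach.** Inputs: 1:1 block randomisation (Randomization and allocation) and 30 subjects (Sample size). Block size b is not stated and is assumed over a range.

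In a 1:1 block of size b, once one member's arm is known, b − 1 members remain, of whom b/2 are in the opposite arm. For any other member of that block:

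P(opposite arm) = (b/2) / (b − 1)

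| Assumed block size | Calculation | Chance of a correct guess |
|---|---|---|
| 2 | 1/1 | 100% |
| 4 | 2/3 | 67% |
| 6 | 3/5 | 60% |
| 10 | 5/9 | 56% |
| 30 (one block) | 15/29 | 52% |

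Without the disclosure the chance is 50%. The information is material only for small blocks. These values are upper bounds, because they assume the guesser knows the block size and which subjects share the block. The article does not say that investigators are given either.

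**5. What limits any bias.**
- The unblinded subject leaves the study, so little further assessment of that subject is exposed.
- Under Data collection and analysis, two blinded research assistants collect the data and complete the case report form.
- Under Blinding, a third party evaluates and processes the data.
- The primary outcome, reduction in serum uric acid, is a laboratory value.

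**The case against.** The case for leaving the text alone is substantial, and much of it stands.

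- **Delay.** A reader might infer that the rule will hold up care. The documents do not show this. The sentence says would be, not must, and sets no quorum, timing or physical meeting. Under Adverse events management, study drug is stopped immediately for any serious adverse event and the ethics committee is told within 24 hours. Neither step waits for the code. What remains is an avoidable dependency for decisions that need the arm.
- **Funders.** A reader might infer that the trial needs its funders blinded. The article never says so and gives them no rating or analysis role.
- **Assignment table.** A reader might infer a breach of the promise to keep the table confidential to the end of the study. That does not follow: one subject's code can be released without opening the table.
- **Whole-trial unblinding.** A reader might take one event to open every allocation. The purpose and consequence sentences point to a single subject.
- **Bias through block-mates.** This needs a possibly drug-related serious adverse event among 30 subjects, small blocks, known block membership, and an informed person rating the block-mates. That chain is thin.
- **Condensed article.** The full protocol, version 1.4, may describe further operational steps. The absence of an out-of-hours route here is therefore no finding. The attendance condition is different, because it is stated.
- **Witnessing as a safeguard.** Witnesses can deter casual code breaks. That is a fair purpose, but the written record already required serves it, and it does not explain why blinded principal investigators should see the arm.

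**Conclusion.** The point holds in a limited form and is minor. The Blinding section states a procedure that works against its own purpose, by attaching an attendance condition to an urgent one-subject step. It also conflicts with the same section's statement that investigators are blinded, and it refers to the trial where one subject is meant.

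The size of any delay cannot be derived from the document. Beyond the affected subject, the blinding cost runs from negligible (52% against 50% for one block of 30) to material (67% for blocks of 4), on the assumption that block size and membership are known. Blinded data collection and a laboratory primary outcome keep the primary comparison largely out of reach. The documents do not support reading this as a demonstrated safety failure, as a breach of a blind on the funders, or as a threat to the primary result.

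**What to change.** Amend the Blinding section as follows.

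1. Replace the reference to unblinding the trial with unblinding the affected subject's allocation.
2. State that the code for that subject alone is released, through the existing interactive randomisation system or by the randomisation centre, to the person managing the event, and that neither the principal investigators nor the funders need be present.
3. State that the principal investigators and funders are told that a break occurred but not the arm, unless a principal investigator is managing the event.
4. State that, where feasible, anyone who learns the arm does not rate judgement-based outcomes in other subjects. This matters because the trial has one centre, and the person managing the event may also see other participants.
5. Keep the written record already required, and add the names or roles of those who learned the arm.

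The cost is protocol wording, since the interactive system already exists. The downside is that the break is no longer witnessed, which the record covers. No sample size, alpha level or analysis changes, and no clinical rule is touched.

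Trial status gives enrolment as March to August 2021, so the change may come too late for these subjects. In that case, report any code break and who learned the allocation, and carry the corrected wording into the larger trial that the article plans.
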